## Abstract

In the absence of information from the visual system, balance is guided by only two of the three afferent systems. If there is no early stimulation of these systems, blind children tend to become passive, which can have a negative impact on muscle tone, coordination and balance. The aim of the present study protocol is to investigate whether transcranial direct current stimulation (tDCS) can enhance the effects of static and dynamic proprioceptive exercises on gait and balance control in children and preadolescents with acquired or congenital visual impairment. This randomized controlled trial will be conducted in three phases, starting with a cross-sectional analysis, followed by a pilot study, and concluding with a full-scale clinical trial. The study will be conducted following approval from the institutional review board of Universidade Evangélica de Anápolis, Anápolis, GO, Brazil (certificate number:4610052.6.0000.5076). The study will be divided into three phases. Phase 1 will be a cross-sectional study to characterize gait, postural control and balance (static and dynamic) in the sample. Phase 2 will be a pilot study that will serve to determine the sample size in Phase 3. Both phases 2 and 3 will employ the same methods and will constitute a randomized, controlled, double- blind, clinical trial. The participants will be randomly divided into four groups: (G1) active tDCS + static proprioceptive exercises; (G2) sham tDCS + static proprioceptive exercises; (G3) active tDCS + dynamic proprioceptive exercises; (G4) sham tDCS + dynamic proprioceptive exercises. The results will be based on evaluations performed on three occasions [preintervention, postintervention (after ten treatment sessions) and 1-month follow-up] and will involve three-dimensional gait analysis as well as assessments of functional mobility functional and balance (static and dynamic). The expected outcomes of this study protocol include determining the postural differences, functional mobility, and static balance between children and pre-adolescents with congenital and acquired visual impairment and enable the establishment of new rehabilitation protocols.

## Introduction

According to the Action Plan of the Vision 2020 Program by the International Agency for the Prevention of Blindness (IAPB), it is estimated that 1.4 million children worldwide have some form of visual impairment (1). The agency reports that the primary causes of childhood blindness include corneal scars, cataracts, glaucoma, retinopathy of prematurity, refractive errors, and low vision, which encompasses untreatable visual impairment and blindness in all regions globally. Spatial orientation and independent mobility without sight present challenges (2, 3). In the absence of visual information, navigation primarily depends on integrating cues related to direction, distance, and speed derived from vestibular and proprioceptive inputs (4, 5). Blind children need to integrate and synthesize information from other senses and must receive consistent and adequate stimulation from an early age to support their typical development without neuropsychomotor deficits (6, 7).

Balance is a result of interactions among the visual, somatosensory, and vestibular systems, which provide feedback to the central nervous system on necessary adjustments. In the absence of visual information, balance is guided by only two of these three afferent systems (7). Thus, visually impaired individuals rely more heavily on vestibular and somatosensory information to maintain balance, whereas sighted individuals primarily rely on visual stimuli (8). To maintain balance and avoid falls, visually impaired individuals exhibit postural deviations from childhood through adulthood and adopt compensatory postures to maintain an upright stance, which influences gait patterns (9, 10). Blind individuals display behavioral strategies in the postural control system that produce increased body sway, enhancing afferent information from remaining senses (11). Interestingly, when blind children are stimulated with proprioceptive exercises, postural control improves, as demonstrated by reductions in sway velocity and displacement of the center of pressure (12).

That low vision in children aged eight to eleven affected postural stability in the standing position as well as the speed of postural adjustments, negatively impacting balance (13). These findings provide valuable insights into the adjustment mechanisms that contribute to maintaining an upright posture in challenging situations. Houwen et al. (14) found that visually impaired individuals exhibited reduced gait speed, shorter stride length, and longer support phase duration during gait compared to sighted individuals. Exercises that stimulate vestibular and proprioceptive pathways are thus crucial for visually impaired individuals. For instance, proprioceptive exercises can improve balance and favor body stability by reducing center of pressure movements or by enabling faster recovery (15).

Proprioception and sensory information from the plantar surface are essential to the maintenance of postural control under typical conditions for blind individuals (16, 17). Blind children who are not stimulated from an early age tend to become passive, with negative impacts on muscle tone, coordination, and balance. Therefore, early intervention is crucial to prevent potential neuromotor delays in these individuals (18).

The combination of motor therapies with methods that stimulate specific areas of the brain, such as the cerebellum, may yield more effective results than motor therapy alone (17, 18). The cerebellum plays a crucial role in motor coordination and balance control, making it a strategic region for interventions aimed at improving posture and gait. According to Zhou et al. (17), transcranial direct current stimulation (tDCS) influences cortical and cerebellar networks during postural control and gait tasks by modulating cortical excitability, which may enhance motor function during cognitive tasks. Recent studies indicate that cerebellar tDCS also promotes neural plasticity and improves motor control in children with neuromotor disorders (19–22). Parreira et al. (20) demonstrated that tDCS can enhance motor evoked potential (MEP) parameters, correlating with improvements in motor control. The MEP reflects corticospinal neuron excitability (23) and is associated with neural plasticity (23). Furthermore, MEP changes extend beyond areas directly stimulated by tDCS (23, 24). However, the effects of cerebellar tDCS on visually impaired children and preadolescents remain poorly understood, underscoring the need to investigate its potential in improving postural control and motor coordination in this population.

This study, therefore, aims to assess whether tDCS can amplify the effects of static and dynamic proprioceptive exercises on gait and balance in children and preadolescents with acquired or congenital visual impairment. The study seeks to correlate differences in outcomes related to gait, static and dynamic balance, and functional mobility between dynamic and static proprioceptive exercises. It also analyzes the specific effects of these exercises on gait, balance, and functional mobility by conducting a comparative analysis of the effects of active vs. sham tDCS, combined with proprioceptive exercises, on the same variables in children and preadolescents with acquired and congenital visual impairment. Our hypothesis is that tDCS combined with static and dynamic proprioceptive exercises may improve gait and balance, as these individuals exhibit deficits in balance, posture, and gait due to a lack of visuomotor coordination. We believe the proposed protocol could enhance gait, balance, and postural control in these individuals by modulating neuroplasticity (23, 24).

## Materials and methods

### Study design

This protocol study is a proposal for a clinical trial study that followed the standard protocol items for clinical trials according to SPIRIT 2013 statement (25). The study will be divided into three phases (Table 1). Phase 1: will comprise a cross-sectional study to characterize the sample's postural control, static and dynamic balance, and gait. Phase 2: will comprise a pilot study with a convenience sample of 6-to-12-year-old children and preadolescents with either acquired or congenital visual impairment and children and preadolescents with normal vision. The objective of the pilot study will be to observe the effects of tDCS on postural control and gait during a proprioceptive exercise protocol. The results of this phase will be used to estimate the sample size of Phase 3, described in Figure 1. Phase 3: will be a randomized, controlled, double-blind, and clinical trial in children and preadolescents with either acquired or congenital visual impairment where we will seek if there will be differences among pre-intervention, post-intervention, and after 1 month of treatment throughout the tridimensional gait analysis, electromyography, functional mobility, and static and dynamic gait assessment.

**Table 1 T1:** Phases, outcome measures, and evaluation of the protocol study.

Phase	Objective	Participants	Primary outcome measures	Secondary outcome measures	Evaluation times
Phase 1: cross- sectional characterization	To characterize gait, balance, and postural control before the intervention.	Children and preadolescents with visual impairment (acquired or congenital blindness) and sighted children (control group).	- Three-dimensional gait analysis (gait speed, stride length, support phase, COP displacement) - Static and dynamic balance assessment - Timed Up and Go (TUG) test - Pediatric Balance Scale (PBS)	- Pediatric Evaluation of Disability Inventory (PEDI)	Baseline assessment (pre- intervention)
Phase 2: pilot study	To assess the feasibility of the protocol and determine the sample size for Phase 3.	Convenience sample of children with acquired or congenital visual impairment.	- Three-dimensional gait analysis - Static and dynamic balance assessment - Timed Up and Go (TUG) test - Pediatric Balance Scale (PBS)	- Electromyography (EMG) - PEDI - G-sensor® analysis for spatiotemporal gait parameters	- Pre-intervention - Post-intervention (after 10 sessions) - 1-month follow-up
Phase 3: randomized controlled trial (RCT)	To test the effectiveness of tDCS combined with static and dynamic proprioceptive exercises on gait, balance, and functional mobility.	Children and pre-adolescents with visual impairment, randomized into 4 groups: G1: Active tDCS + static exercises G2: Active tDCS + dynamic exercises G3: Sham tDCS + static exercises G4: Sham tDCS + dynamic exercises	- Three-dimensional gait analysis - Static and dynamic balance assessment - Timed Up and Go (TUG) test - Pediatric Balance Scale (PBS)	- Electromyography (EMG) - PEDI - G-sensor® analysis for spatiotemporal gait parameters	- Pre-intervention - Post-intervention (after 10 sessions) - 1-month follow-up

Timeframe of development of study. G1 (Group 1), active tDCS + static proprioceptive exercises; G2 (Group 2), sham tDCS + static proprioceptive exercises; G3 (Group 3), active tDCS + dynamic proprioceptive exercises; G4 (Group 4), sham tDCS + dynamic proprioceptive exercises; *t*, time in months.

**Figure 1 F1:**
[figure not shown]
Flowchart of study design based on CONSORT 2010 guidance for protocols of clinical trials. G1 (Group 1), active tDCS combined with static proprioceptive exercises; G2 (Group 2), sham tDCS combined with static proprioceptive exercises; G3 (Group 3), active tDCS combined with dynamic proprioceptive exercises; G4 (Group 4), sham tDCS combined with dynamic proprioceptive exercises; *t*, time in months; *n*, sample number.

### Ethical approval

The proposed study will be conducted following the guidelines and regulatory norms stipulated by the National Board of Health in October 1996 and updated in Resolution 466 of 2012 governing research involving human subjects in Brazil. The study will be conducted following approval from the institutional review board of *Universidade Evangélica de Anápolis*, Anápolis, GO, Brazil (certificate number: 4610052.6.0000.5076). The study protocol was registered in the *Registro Brasileiro de Ensaios Clínicos* (ReBEC) (number RBR-3chg6v5) available in https://ensaiosclinicos.gov.br/.

### Sample size and recruitment

The sample size for Phase 3 of the study will be estimated based on the minimal difference between the mean of the analysis of variance results obtained from both gait speed and the displacement of the center of pressure (COP) as the primary outcome obtained in the groups of the pilot study (Phase 2) considering the primary outcome. Thus the sample size will be estimated with a unidirectional alpha of 0.05 and an 85% statistical power. The sample determined by the calculation will be increased by 20% to compensate for possible dropouts. Since this is a proposal study for a clinical trial, for the part of the study, the main objective of the study will be to establish an effect size for tDCS treatment in association with proprioceptive exercises. This is independent of the number of volunteers but allows us to estimate the number that would be required to achieve statistical significance depending on the effect size we observe.

Children and preadolescents with acquired or congenital visual impairment will be sent by healthcare providers of the *Centro Municipal de Atendimento à Diversidade* [CEMAD (Municipal Diversity Care Center)] in the city of Anápolis, Brazil. Preselected individuals will then be screened, with the collection of personal information and anthropometric measures. Congenital and acquired blindness will be characterized based on the classification of the degree of visual impairment proposed by the World Health Organization, the International Statistical Classification of Disease, and the 10th Edition of the International Classification of Disease, in which visual acuity <20/400 or <20/200 in the better eye is classified as visual impairment (26, 27).

The study will be divided into three phases. The results of Phase 2 will serve as the basis for Phase 3. Phase 3 was designed according to updated guidelines for reporting parallel group randomized trials CONSORT, 2010 (28). A convenience sample will be used in the first phase, composed of 10 male and female children and preadolescents with acquired or congenital visual impairment between 6 and 12 years of age, who will be recruited from CEMAD in the city of Anápolis, and a control group of 10 sighted male and female children and preadolescents in the same age range, who will be recruited through informal invitations. The visually impaired patients will be referred with a medical diagnosis performed by an ophthalmologist. These 20 individuals will be used to characterize the gait pattern, balance, and functional mobility. The second phase will be a pilot study conducted with the same methods as the main study and will provide data for the calculation of the sample size (Figure 1). To determine differences in gait pattern, balance, and functional mobility subjects with blindness will perform the assessment and tests with/without a guide stick and when wearing shoes and while barefoot.

As this research involves children and pre-adolescents, parents and/or guardians will be consulted in advance to clarify the research objectives, as well as risks and benefits, and those who accept to participate in the research will sign a consent form through the Adult Consent Form subscription. Children and pre-adolescents will also be informed about the objectives and purposes of the research, which, if they also agree, must sign the Child Assent Form developed in a specific language for the age group. At the end of the study, subjects from the sham group will receive active tDCS as a form of treatment and adherence to the study. Finally, if a patient decides to withdraw from the follow-up, the reasons for the withdrawal will be recorded for the subsequent analysis in the interpretation of the results.

### Eligibility criteria

To be included in the study, children and preadolescents must have any abnormalities of the visual system that let them to a total blindness such as: retina disorders, glaucoma, macular degeneration, retinitis pigmentosa, toxoplasmosis, cataracts, detached retina, abnormalities of the optic nerve, Leber's amaurosis, and astrocytoma. For exclusion criteria we will set for: use of medication affecting the central nervous system, balance or coordination, symptoms of vertigo or dizziness, clinical condition affecting balance and gait, surgery of the lower limb, vascular and sensory disease. Additional exclusion criteria that will be considered for tDCS are: frequent migraine/headache, metallic implant in the head or neck, scalp or skin condition and seizures.

### Randomization and allocation to groups

Randomization will take place in blocks. Participants and investigators will be blind to the tDCS condition allocation. Individuals who meet the eligibility criteria will be randomly allocated to one of the four study groups using a digital randomization platform (http://www.randomization.com). An opaque and sealed envelopes will be used to conceal group information. After signing the informed consent, individuals will choose an envelope with the name of the group to which they will be assigned in phases 2 and 3. This step will be managed by a third person who is not part of the study. The groups will be divided according to the type of therapy: Group 1 (G1)—active tDCS combined with static proprioceptive exercises; Group 2 (G2)—sham tDCS combined with static proprioceptive exercises; Group 3 (G3)—active tDCS combined with dynamic proprioceptive exercises; Group 4 (G4)—sham tDCS combined with dynamic proprioceptive exercises.

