#### Masking

Participants, therapists, and assessors involved in the study will be blinded to the treatment allocation. During the intervention, both active and sham tDCS conditions will have the electrodes applied in the same manner. However, in the sham condition, the stimulation will only be applied for the first 30 s to mimic the sensation of tDCS, after which no current will be delivered for the remaining session time.

The therapists administering the intervention will not have access to the allocation sequence and will perform the same proprioceptive exercises for all participants, regardless of the group. To prevent any bias, the individuals responsible for collecting and analyzing the data will also be blinded to group allocation.

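### Having each participant choose an envelope that contains a group name conflicts with the blocked, platform-generated allocation and opens an avoidable route to disclosing active or sham tDCS

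*Protocol article*

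**What the plan says.** The section on randomization and allocation to groups in the protocol article makes these statements:

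- The method: "Randomization will take place in blocks", with eligible individuals "randomly allocated to one of the four study groups using a digital randomization platform". No block size is given.
- Concealment: "An opaque and sealed envelopes will be used to conceal group information".
- Assignment: after consent, "individuals will choose an envelope with the name of the group to which they will be assigned in phases 2 and 3".
- Who runs it: "This step will be managed by a third person who is not part of the study".
- What a group name means: each of the four names fixes the stimulation condition as well as the exercise type, for example "Group 2 (G2)—sham tDCS combined with static proprioceptive exercises".
- Blinding: "Participants and investigators will be blind to the tDCS condition allocation".

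The Masking section adds: "Participants, therapists, and assessors involved in the study will be blinded to the treatment allocation". Two other places bear on the point. The phase 3 row of Table 1 defines G2 as active with dynamic exercises and G3 as sham with static exercises, whereas the randomization section and the Table 1 footnote define G2 as sham with static and G3 as active with dynamic. The closing paragraph on gait analysis and electromyography says that the principal investigator alone will know the allocation, and concedes that patients and therapists are unlikely to remain blinded.

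**The concern.** A blocked list controls balance only if assignments are used in list order. A participant's free pick is a second, different mechanism. If it decides the group, the platform's sequence has no role, and nobody can later check that the allocations made match the list.

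The second issue is what the envelope holds. The participant's side is handed something that contains a group name, and every group name stands for active or sham. Active against sham is the trial's central comparison. Several primary outcomes (gait speed, Timed Up and Go, Pediatric Balance Scale) depend on effort and can respond to expectation. A condition disclosed at allocation cannot be undone in the analysis.

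Balance part-way through also matters. The sample size section takes the phase 3 sample size from the pilot groups, and the statistical analysis section plans an interim look at the primary outcomes around phase 2.

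**Working it through.** **1. The two mechanisms side by side.** Platform and blocks: the list decides, and its order is fixed in advance. Chosen envelope: the pick decides, and its order is whatever the draws produce. Both hold only if the choice is nominal, and the text does not say that. It mentions no numbering, no fixed opening order and no restriction to the current block. With such a restriction, balance per block would survive, but the generated order within each block would still be lost.

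**2. Size of imbalance (illustration).** The article gives no sample size for phase 2 or 3, no block size and no pool size, so there is no stated figure to reproduce. Assume N = 40 envelopes, K = 10 per arm, n = 20 drawn without replacement.

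- One arm's count: mean = n × K/N = 5. Variance = n × (K/N) × (1 − K/N) × (N − n)/(N − 1) = 20 × 0.25 × 0.75 × 20/39 = 1.92, so SD = 1.39.
- A given pair: the four counts sum to a constant, so each covariance is −1.92/3 = −0.64. The variance of the difference is 2 × 1.92 + 2 × 0.64 = 5.13, so SD = 2.26. With continuity correction, P(gap ≥ 3) ≈ P(|Z| > 2.5/2.26) ≈ 0.27. Exact enumeration gives 26.9%.
- Largest against smallest arm: simulation (20,000 draws) gives a mean gap of 3.3 and P(gap ≥ 3) = 64.7%. Exact enumeration gives 64.2%.

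Other assumed pool sizes, largest against smallest arm, by simulation:

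| Envelopes | Drawn | Mean gap | P(gap ≥ 3) |
|---|---|---|---|
| 24 | 12 | 2.5 | 43% |
| 40 | 20 | 3.3 | 65% |
| 80 | 40 | 4.6 | 83% |
| 24 | 16 | 2.4 | 37% |
| 40 | 32 | 2.6 | 46% |
| 80 | 64 | 3.7 | 73% |

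The last three rows represent recruitment stopping at no more than 80% of the pool. With blocks of 4 used in order, the gap is 0 at each completed block and at most 1 in between. If the whole pool is drawn, the arms end equal under either method.

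**3. What imbalance costs in precision.** Pool the two active arms against the two sham arms, again with N = 40 and n = 20. The active count has variance 20 × 0.5 × 0.5 × 20/39 = 2.56. Mean efficiency relative to an equal split is 1 − 4 × 2.56/20² = 0.974, about 97%. A split of 13 to 7 gives 1 − 4 × 3²/20² = 0.91. The loss in that comparison is small.

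**4. The blinding route.** Set the assignment sentence beside the definitions of G1–G4. Knowing the group name together with its definition is knowing active or sham. The article describes no neutral code and does not say who opens or reads the envelope. The outside person shields study staff, but nothing stated shields the participant or guardian. The eligibility criteria require total blindness, so any printed name would have to be read to the child by someone else.

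**5. The label itself.** Because Table 1 and the randomization section exchange the meanings of G2 and G3, a bare label is not a dependable code for whoever sets the stimulator.

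**The case against.** The strongest reply is that the wording is loose rather than wrong. The envelopes are opaque and sealed, so the name is inside, not on show. A pick from such envelopes can still be a chance draw that staff cannot foresee. No sentence says that the family opens or reads the contents, and an outside person manages the step. A bare label means something only to a person who holds the key. The envelopes might be batched by block, and numbering is a detail that an article may leave to the full protocol. The imbalance figures rest on assumed inputs, the efficiency loss is minor, and if phase 2 has its own envelope set that is fully drawn, its arms end equal. The article also already concedes that patients and therapists are unlikely to stay blinded.

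Much of this stands, and it limits the point. A reader might infer that every family sees its condition, that blinding is defeated, that concealment has failed or that selection bias is present. The documents support none of these. They also do not establish that the blocks are certainly lost.

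What does not stand is the claim that this is only missing detail. The article states a positive rule, that the individual chooses, and it does not fit the blocked list stated in the same section. The concession about blinding is no reason to leave open a disclosure route that can be closed easily.

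**Conclusion.** The point holds as an internal conflict in the allocation procedure together with an avoidable risk of unblinding. If the pick decides the group, the trial loses its generated block order and the audit trail for it. Interim balance is then not assured unless picks are confined to the current block.

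Under the assumed 40 envelopes, a gap of 3 or more after 20 picks has a probability of about 65% for largest against smallest arm and about 27% for a given pair. Blocks of 4 in order give at most 1. These figures move with the assumed pool size, and the imbalance disappears if the pool is exhausted. Its effect on precision is modest, so the main statistical harm is loss of a verifiable sequence.

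On blinding, disclosure follows if the envelope is opened by or read to the participant or guardian. The text permits this but does not say that it will happen. The different definitions of G2 and G3 are a plain contradiction in the article.

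**What to change.** Replace the sentence on choosing an envelope with wording such as:

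> After consent, the independent third person opens the next sequentially numbered, opaque, sealed envelope in list order. The participant, family, therapist and assessor are told only the exercise type and a neutral code. Active or sham is set from that code by a person not involved in treatment or assessment.

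Two reconciliations go with it:

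- State who holds the code list. The randomization section has investigators blind and an outside person managing the envelopes, while the paragraph closing the gait analysis section has the principal investigator alone knowing the allocation. That section also has the principal investigator locating the marker landmarks, so the answer matters for assessor blinding.
- Make the definitions of G1–G4 the same in Table 1, its footnote, the figure legend and the text.

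The third person is already in the plan. The cost is preparing numbered envelopes and a code list, and arranging for the stimulator to be set from the code. The article does not say whether the device has a coded sham mode, so this last item may need more than a change of wording. All of it must be in place before the first phase 2 allocation.
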